PROMs can be generic or disease-specific, and each has several advantages and disadvantages [38]. Generic measures are used to compare outcomes across different populations and interventions, particularly for cost-effectiveness studies and health system decision-makers. Disease-specific measures assess the health status of a specific patient population and may be more sensitive for the detection and quantification of changes that are important to clinicians or patients. A common recommendation in clinical research with PROMs is to combine both a generic and a disease-specific measure for use in a particular patient population, especially when PROMs are used to monitor health and how it changes over time. The presumed benefit of this combination is to broaden the scope of measurement and allow for different uses of the measures (e.g., comparison within versus across disease populations). However, evidence to support this recommendation is limited. In fact, in a study examining the usefulness of generic and disease-specific measures of health status in patients with Alzheimer’s, the EQ-5D (a generic measure) was found to be a suitable alternative to a disease-specific measure of health [39]. Another study reported that generic and disease-specific measures performed similarly in assessing changes in HRQL in patients with kidney failure requiring hemodialysis [40]. There is usually some level of overlap between generic and disease-specific measures, and the need for combining both types of measures depends on the target patient population and the constructs assessed by each measure. Given the workload associated with collecting and using PROM data in clinical settings, it is imperative to explore whether one single PROM is sufficient to improve patient-provider communication, processes of care, and ultimately patient outcomes, before recommending the use of a combination of generic and disease-specific measures.

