## Methods

### Study design

To date, the effect of PROMs on patient outcomes were generally assessed in conventional parallel-group RCTs of individuals. Few convincingly demonstrated benefits to patient-important outcomes, which might be in part due to contamination effects and small sample sizes [47]. This study uses a cluster RCT design, with clustering occurring at the level of individual hemodialysis units, to reduce potential contamination between the study groups (Fig. 1). EMPATHY is an open-label RCT, since blinding is not feasible [48]. Consequently, research staff, clinicians, and all patients are aware of group allocation. Dialysis units, stratified by three regions (Northern Alberta, Southern Alberta, and Ontario), were randomly allocated using random number sequences with all units from a region randomized on the same day. Dialysis units were allocated in a 1:1:1:1 ratio into four groups:
Group 1: Patients complete ESAS-r: Renal or IPOS-RenalGroup 2: Patients complete EQ-5D-5LGroup 3: Patients complete both ESAS-r: Renal or IPOS-Renal and EQ-5D-5LGroup 4: Usual care (i.e. the control group). To assess study outcomes, patients complete the PROMs at baseline, 6 and 12 months, but these data are not reported back to clinicians or patients.

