### Sample size and power

The EMPATHY trial is a pragmatic clinical trial with a sample size determined based on eligibility of hemodialysis units and its encompassing patients. Our intention was to enroll all eligible dialysis units within the province of Alberta, and a sample of eligible units in Ontario. Therefore, we did not calculate an optimal sample size for adequate power to detect statistical significance. From 44 dialysis units, we will be utilizing data from approximately 3000 patients. Based on an estimated intraclass correlation of 0.1 and a standard deviation for the CAT (primary outcome measure) of 0.74 (based on pilot data from HD patients in Alberta), this will provide 80% power to detect an effect size of 0.23 with a two-tailed test at typical level of significance, α = 0.05 [59]. While this is a small effect size for the primary outcome, we are nonetheless confident in the design, given that this is a pragmatic quality improvement study, involving 44 dialysis units from three renal programs with several secondary objectives related to patient experience and outcomes.

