### Quantitative trial data analysis

The primary analysis will assess change in the overall CAT score, between study groups from baseline to 12 months using a linear mixed effects model, with the mean CAT for the dialysis unit at baseline as a fixed effect covariate, and dialysis unit (cluster) as a random intercept. Ideally, analysis should use individual patients’ baseline CAT and follow-up CAT rather than the unit mean baseline CAT to compute change over time. However, due to concerns by the regional renal programs to maintain anonymity of experience data as well as the natural drop-in and drop-out of patients in the dialysis units due to patient deaths and initiation of new patients onto dialysis, individual CAT surveys were made completely anonymous. As such, our primary analytic plan will be based on changes in mean CAT score at the unit level, from baseline to 12 months. The primary analysis will be based on all of the PROMs intervention groups combined compared to the control (no PROMs intervention) group as fixed effects. Any units that drop-out after randomization but prior to initial data collection will be excluded. We will employ last observation carried forward methods to impute missing data where appropriate. As one of our secondary objectives, assessing differences between specific and generic PROMs, we will compare the individual interventions groups (i.e., ESAS-r: Renal /IPOS alone, EQ-5D-5D alone, or the combination) to the control group.

As part of our secondary analyses, we will also compare the proportion of patients reporting symptoms/problems on the ESAS-r: Renal or IPOS-Renal and EQ-5D-5L and the management of such symptoms/problems. Through clinical records, we will link PROMs scores with the use of specific symptomatic treatments as per the treatment aids. We will obtain medication lists, allied health referrals, and chart notes to capture how symptoms are being treated. Because the PROMs data will be collected as part of the clinical record, and linked with individual patient-level data, we will be able to analyze these data using logistic mixed-effects regression models adjusting for individual patient-level covariates. Each renal program (i.e., AKC-N, AKC-S and ORN) will be analyzed separately then we will use meta-analyses to analyze the data from each renal program.

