## Discussion

The evaluation of PROM interventions such as those described in this protocol can be challenging given the nature of clinical practice in busy hemodialysis units, the variations in organization and clinical workflow across units, as well as regional programs. We will study the implementation of PROM interventions in real-world health settings. Thus, we will adopt a pragmatic approach and accept the necessary variations in implementation, while attempting to retain as many of the core elements of the interventions across the programs. Furthermore, given the desire to maintain anonymity of patient-reported experience, our primary analytic strategy will be limited to comparison of the outcome measures at the group level. These pragmatic approaches to the design of this implementation study limit the rigour of the evaluation of the efficacy of PROM interventions, but on the other hand, enhance our evaluation of real-world effectiveness. Along with the planned qualitative assessments, the information gained from this implementation trial will provide valuable information for the regional dialysis programs in enhancing and sustaining the PROM interventions in the most appropriate manner.

A question that is often raised with the implementation of PROM programs is the choice of the measures. We are choosing to implement a combination of specific and generic measures. While a secondary objective is to compare these types of measures, it is possible that the differences (e.g., breadth or scope) between measures matter less than either approach simply serving as a mechanism for engaging patients and clinicians in a more focused discussion on symptoms or problems. This is the intention with our primary analytic strategy of combining the intervention groups to compare against the control group with no PROM intervention. There may be other reasons, beyond the patient-clinician interaction, however, that guide decisions on the choice of measures. For example, programs may be interested in evaluating the overall quality and efficiency of services, and may therefore be interested in a measure that provide data to support economic evaluation. In this case a generic preference-based measure such as the EQ-5D provides an overall index score compatible with that purpose, which may not be available with measures assessing symptom burden.

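### If the three PROM interventions differ in effect, a single any-PROM indicator makes the primary CAT test conservative; a four-group model with an averaged contrast avoids this at almost no cost

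*Protocol article*

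**What the plan says.** Study design: "Dialysis units were allocated in a 1:1:1:1 ratio into four groups": disease-specific PROM, generic PROM, both, and usual care.

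Quantitative trial data analysis: the primary analysis is a linear mixed model for the CAT, "with the mean CAT for the dialysis unit at baseline as a fixed effect covariate, and dialysis unit (cluster) as a random intercept". The primary comparison is "based on all of the PROMs intervention groups combined compared to the control (no PROMs intervention) group as fixed effects". No term for the individual PROM group is described in that model. Comparing each PROM group with control is a secondary analysis.

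Discussion: the pooling is deliberate. The article refers to "our primary analytic strategy of combining the intervention groups to compare against the control group", and explains that the choice of measure may matter less than having any measure to focus the conversation.

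Sample size and power: the article gives the size of the trial as "From 44 dialysis units, we will be utilizing data from approximately 3000 patients" and the inputs to the power statement as "Based on an estimated intraclass correlation of 0.1 and a standard deviation for the CAT (primary outcome measure) of 0.74". From these it claims "80% power to detect an effect size of 0.23 with a two-tailed test at typical level of significance".

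**The concern.** Units are randomised to four groups, but the primary comparison has two. If the model holds one any-PROM indicator, a true difference among Groups 1, 2 and 3 can only go into the between-unit variance. That enlarged variance then sets the standard error of the whole contrast, including the part from the control units, which carry no such differences. The interval over-covers, and a true average benefit is more easily missed.

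This matters because the trial has a stated interest in whether the measures differ. The background says "it is imperative to explore whether one single PROM is sufficient to improve patient-provider communication", and the first secondary objective compares disease-specific with generic PROMs. The number of units was set by availability, so power lost here cannot be recovered by recruiting more units.

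**Working it through.** **Inputs from the article.** 44 units, about 3000 patients, SD 0.74, ICC 0.1, two-sided α 0.05, allocation 1:1:1:1.

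**Assumptions.**
- 11 units per group, so 33 PROM units against 11 control units. The counts per group are not given.
- Equal unit sizes, so the mixed model can be checked on unit means.
- Correlation ρ of true unit means between baseline and 12 months of 0.5 to 0.8.
- The spread of true effects among the PROM groups is varied, because the article gives none.
- 0.23 is read as CAT points. The article does not say whether it means CAT points or SD units.

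**The plan's own figure.**
- Patients per unit: 3000/44 = 68.2.
- Variance of a unit mean: 0.1 × 0.74² + 0.9 × 0.74²/68.2 = 0.0548 + 0.0072 = 0.0620 (SD 0.249).
- SE for 33 against 11 units, no baseline adjustment: 0.249 × √(1/11 + 1/33) = 0.0867.
- Power at 0.23: 75.6% (normal approximation) or 73.5% (t, simulated).

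The stated 80% is therefore not reproduced for this comparison. In SD units, power would be 50.1%. That is a separate matter and does not affect what follows.

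**Size of the inflation with the planned baseline covariate.** Let σ² be the residual variance of a unit mean after adjustment, and dᵢ the deviation of PROM group i's effect from the average of the three. Residual degrees of freedom are 44 − 3 = 41 with one indicator and 44 − 5 = 39 with four groups. The one-indicator model estimates a residual variance of about σ² + 11 Σdᵢ²/41, so

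SE ratio ≈ √(1 + 11 Σdᵢ² / (41 σ²)).

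The correlation of observed unit means is ρ × 0.0548/0.0620, and σ² = 0.0620 × (1 − r²):
- ρ = 0.5: r = 0.442, σ² = 0.0499
- ρ = 0.8: r = 0.707, σ² = 0.0310

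| True effects (CAT points) | Σd² | 11Σd²/41 | SE ratio, ρ = 0.5 | SE ratio, ρ = 0.8 |
|---|---|---|---|---|
| equal | 0 | 0 | 1.00 | 1.00 |
| average ± 0.10 | 0.02 | 0.0054 | 1.05 | 1.08 |
| 0.3, 0.3, 0 | 0.06 | 0.0161 | 1.15 | 1.23 |
| average ± 0.20 | 0.08 | 0.0215 | 1.20 | 1.30 |

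**Power by simulation with the covariate (one indicator against four-group contrast).**
- Equal effects of 0.2: 88.5% against 88.3% (ρ = 0.8). No loss.
- Effects 0.1, 0.2, 0.3: 3 to 4 points lower.
- Effects 0.3, 0.3, 0: 59% against 70% (ρ = 0.5) and 78% against 89% (ρ = 0.8). Coverage of the nominal 95% interval is 97.4% to 98.2%.
- 0.23 ± 0.20: 69% against 81% (ρ = 0.5) and 86% against 95% (ρ = 0.8).

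**Without the covariate, average effect 0.23.**
- No spread: 73.5% against 73.4%.
- ±0.10: 71.0% against 73.7%.
- ±0.20: 62.6% against 73.6%.

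**Direction of the error.** With an average effect of zero and no covariate, the type I error of the one-indicator test is 5.1% with no spread, 4.1% at ±0.10 and 2.4% at ±0.20. The four-group contrast stays at about 5%. The pooled estimate averages 0.23 in every scenario with a true average of 0.23.

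**The case against.** **The coding is not stated.** The wording fixes the comparison, not how the factor enters the model. A four-level factor with an averaged contrast would also fit it, and a condensed article may leave such detail to an analysis plan that is not shown. This stands in part: the one-indicator model is the natural reading, not a certain one. If the sponsor already intends the four-group model, one sentence settles the point.

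**The pooling is deliberate, and the document leans towards similar effects.** The background cites a study in which generic and disease-specific measures performed similarly in hemodialysis patients, and the Discussion expects that differences between measures may matter little. This stands against any claim that a large loss is likely. It does not justify the coding: it is a reason to ask about any PROM against none, and the averaged contrast asks exactly that.

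**Differences among PROMs have their own secondary analysis.** True, but that analysis does not change the standard error of the primary test.

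**Stronger readings.** A reader might infer that the primary test is invalid, or that it loses power whatever the truth. Neither is supported. Any error is conservative, the estimate is unbiased with equal group sizes, and with equal effects nothing is lost. Pooling also has more power than a single PROM group against control (75.6% against 58.2% at 0.23, normal approximation, no covariate). Nor does the statement about whether one PROM is sufficient predict that the effects differ.

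**Conclusion.** The point holds as an avoidable and conditional inefficiency in a valid test. If the primary model has a single any-PROM indicator, its standard error is too large whenever the three PROM effects differ:
- **Equal effects:** no loss.
- **Spread of ±0.10 CAT points:** SE 5% to 8% larger, about 2 to 4 points of power.
- **Spread near the size of the effect:** SE 15% to 30% larger, about 9 to 12 points of power.

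The last case is not one the document predicts, so the modest figures should be read first. The sizes rest on the assumed 11 equal-sized units per group and ρ of 0.5 to 0.8. A higher ρ raises the relative SE inflation, because the covariate removes other variance but not the differences among PROM groups.

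**What to change.** In Quantitative trial data analysis, state that study group enters the primary CAT model as a four-level fixed effect. Define the primary test as the contrast (1/3, 1/3, 1/3, −1): the equal-weight mean of Groups 1 to 3 minus Group 4. Leave the baseline covariate, the unit random intercept and the primary question as they are.

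The cost is one sentence and two denominator degrees of freedom (41 to 39), under half a point of power when the effects are equal. No new data are needed. The contrast also fixes equal weighting of the three PROM groups if their numbers of units turn out unequal.

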### Interventions

Groups 1–3 will collect their allocated PROM(s) from all eligible patients every 2 months, for 12 months (a total of 7 assessments). PROMs are administered by pen and paper or through an electronic platform on a tablet in accordance with hemodialysis unit resources. In Alberta, the electronic medical records (EMRs) generate a PROM report card with a symbol scheme for nurses to follow up with clinical management where applicable. The symbol scheme comprises of a check mark for no problems/symptoms (ESAS-r: Renal = 0, IPOS-Renal = 0, EQ-5D-5L = 1) a caution sign for mild problems/symptoms (ESAS-r: Renal = 1–3, IPOS-Renal = 1, EQ-5D-5L = 2) and a stop sign for moderate-severe symptoms/problems (ESAS-r: Renal = 4–10, IPOS-Renal = 2–4, EQ-5D-5L = 3–5). The PROM report card is printed and added to the patient’s medical chart for review by clinicians (i.e., nurses, nephrologists, and allied health professionals). The report displays each patient’s most recent PROM scores in comparison with their previous scores, much like lab test results. A sample PROM report card is shown in Fig. 2. In Ontario, EMRs do not have report card capabilities and units store the paper-completed PROM questionnaires in the patient’s medical chart, along with previously completed questionnaires for review by clinicians and the patient. In all locations, PROMs are accompanied by treatment aids for some symptoms assessed (pain, pruritus, restless legs, sleeping problems, tiredness, nausea, shortness of breath, anxiety, and depression). Patients are also offered a copy of their PROM report card (if possible) and patient-facing self-management guides for symptom management. This trial is intended to generate evidence on the implementation within the health systems. While we will aim to maintain the study design and key elements of the intervention as consistently as possible, we will allow for the interventions to be tailored to local health systems, accommodating considerations such as the clinical work flow, information systems and capabilities, and internet/WiFi access (Table 1).

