### Primary and secondary outcome measures

The *primary outcome* in this study is patient-provider communication, which is assessed using a modified version of the Communication Assessment Tool (CAT) [55].

*Secondary outcomes* include:
HRQL, assessed using the EQ-5D-5L. [46].Symptom burden, assessed using the ESAS-r: Renal [44] or IPOS-Renal [45] and symptom management through the EMR.Anxiety and depressive symptoms, assessed using the Generalized Anxiety Disorder 2-items questionnaire (GAD-2) [56] and the Patient Health Questionnaire 2-items (PHQ-2) [57], respectively.Patient experience with their disease management, assessed using the Patient Assessment of Chronic Illness Care 11-items questionnaire (PACIC-11) [58].Healthcare utilization (e.g., physician, emergency department and hospitalization), assessed through linkage with provincial administrative health care databases at the individual patient-level.

Demographic characteristics and the outcome measures are collected at baseline, 6-months, and 12-months. Data on medical history, dialysis history, and clinical measures are collected from patient charts.

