### Economic evaluation

A cost-effectiveness analysis will be employed of the different study groups, compared to the usual care group as the reference case. The incremental costs and incremental QALYs of the different interventions relative to the usual care group will be compared to calculate incremental cost per QALYs gained ratios [60, 61]. Costs will be estimated for patients in the different study groups, including treatments received by patients, taking the perspective of the provincial health care system, personnel costs for training and delivery of the PROMs assessments, and subsequent health care utilization for patients in each of the study groups. Health care utilization will be estimated through linkage with provincial administrative health care databases at the individual patient-level. Costs associated with provision of the intervention, including training and nursing time, will be estimated through observations for time and valued using standard staffing wage scales for the respective geographic regions. QALYs will be calculated based on changes in the EQ-5D-5L index score, using the Canadian preference weighting [62]. Discounting or inflationary factors will not be applied as the analysis will be limited to the period of the study itself (i.e., 12 months). Self-reported survey and clinical data will be linked to administrative data on healthcare utilization (e.g., number of hospitalizations, number of emergency department visits, number of family physician and specialist visits, cost), one-year prior and one-year after the intervention starts. Linkage to lab and medication datasets will also be performed where available.

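### The only stated missing-data method, last observation carried forward, has no patient-level use for the anonymous primary outcome; the one workable form copies old unit means

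*Protocol article*

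**What the plan says.** All the relevant statements on the primary outcome stand in one paragraph of Quantitative trial data analysis.

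- **Anonymity.** The article explains that "individual CAT surveys were made completely anonymous". One reason is the renal programs' wish to protect experience data. The other is the "natural drop-in and drop-out of patients in the dialysis units due to patient deaths and initiation of new patients onto dialysis".
- **Level of analysis.** As a consequence, "our primary analytic plan will be based on changes in mean CAT score at the unit level, from baseline to 12 months". The model is a linear mixed model with the unit's baseline mean CAT as covariate and unit as random intercept.
- **Lost units.** "Any units that drop-out after randomization but prior to initial data collection will be excluded". Nothing is said about units that are lost later.
- **Missing data.** "We will employ last observation carried forward methods to impute missing data where appropriate". No outcome, level (patient or unit) or criterion is given.

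Elsewhere:

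- Primary and secondary outcome measures: "Demographic characteristics and the outcome measures are collected at baseline, 6-months, and 12-months".
- Interventions: groups 1-3 complete their PROMs "every 2 months, for 12 months (a total of 7 assessments"). Under Study design, the control group completes them only at baseline, 6 and 12 months.
- Economic evaluation: "QALYs will be calculated based on changes in the EQ-5D-5L index score". That section mentions neither missing values nor death. Table 2 places dead at 0 on the index scale.

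**The concern.** Carrying a last observation forward needs an earlier value from the same person. With anonymous CAT surveys that value cannot be identified, so the stated method and the stated data structure do not fit together at patient level. What remains is to fill a unit's empty 12-month slot with its own earlier mean. Units that leave after initial data collection are not excluded, so this is the only route the text offers for them. If the baseline mean is copied, the unit's outcome equals its own covariate and its change is exactly zero, yet it enters the model as data.

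At stake are the size of the primary effect and the width of its interval. Outcomes that can be linked to patients, such as EQ-5D-5L and the QALYs derived from it, meet the general weakness of single imputation and also an open question about patients who die.

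**Working it through.** **1. The plan's own figure.** The article states no figure for missing data. Its only benchmark is 80% power for an effect of 0.23 (44 units, about 3000 patients, intraclass correlation 0.1, SD 0.74, two-sided 0.05; Sample size and power).

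- Mean unit size 3000/44 = 68.18; design effect 1 + 67.18 × 0.1 = 7.718; effective N = 3000/7.718 = 388.7.
- Pooled intervention against control, 3:1: SE = 0.74 × √(1/97.2 + 1/291.5) = 0.0867. Detectable effect (1.960 + 0.842) × 0.0867 = 0.243; power at 0.23 is 75.6%.
- A 1:1 split gives a detectable effect of 0.210 and power of 86.5%.

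The stated 0.23 lies between these two values and is not reproduced exactly. That is a separate matter. Here 0.23 serves only as a reference effect, and the factors below apply to any effect.

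**2. Bias in the primary contrast.** Let p be the share of units with a copied value (equal across arms, units weighted equally) and c the share of the 12-month effect already present in the copied value. Then

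expected effect = true effect × [1 − p(1 − c)].

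| p | baseline copied (c = 0) | 6-month mean with half the effect (c = 0.5) |
|---|---|---|
| 10% | 0.23 × 0.90 = 0.207 | 0.23 × 0.95 = 0.2185 |
| 20% | 0.23 × 0.80 = 0.184 | 0.23 × 0.90 = 0.207 |
| 30% | 0.23 × 0.70 = 0.161 | 0.23 × 0.85 = 0.1955 |

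With c = 1 there is no bias. With c above 1 (an effect that wanes after 6 months) the estimate is inflated. If the shares differ between arms and CAT drifts over time for other reasons, copying baseline adds about (difference in share) × (drift). Differences of 5-20 points with a drift of 0.1-0.3 give 0.005-0.06, in either direction.

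All values of p and c are assumptions. For scale, each arm has about 44/4 = 11 units, so one copied unit is about 9% of an arm, and 10-30% of 44 units is about 4 to 13 units.

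**3. Understated uncertainty.** Take a simple change-score analysis of n units with change variance σ², copy baseline in a share f, and ignore the extra spread from mixing zero and real changes. The variance of the mean change then appears as (1 − f)σ²/n, whereas the units actually observed support σ²/[(1 − f)n]. The ratio of standard errors is 1 − f, or 0.90 to 0.70 for f = 10-30%. In this simple case estimate and standard error shrink together, so the test statistic moves little. The harm falls on the estimate and its interval, which is too narrow and centred too close to zero.

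**4. Linked outcomes.** If a utility u were carried to month 12 for a patient who died at month t, that patient's QALYs would be overstated by u(12 − t)/12. For t = 6 and u = 0.6-0.8 this is 0.30-0.40. With an assumed 12-month mortality of 10-20%, spread evenly, the mean overstatement within an arm is mortality × u × 0.5: from 0.10 × 0.6 × 0.5 = 0.03 to 0.20 × 0.8 × 0.5 = 0.08 QALY per patient. The economic evaluation uses incremental QALYs, where the error is (difference in mortality) × u × 0.5. With equal mortality and similar utilities it largely cancels.

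If the routine PROM assessments feed these outcomes, a carried value can be up to 2 months old in the intervention arms when a patient leaves, but up to 6 months old in control. The imputation would then differ by arm.

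**The case against.** The strongest reply is that the sentence ends with a qualifier limiting the method to cases where it is suitable. On that reading the CAT is simply outside its scope, and the mixed model is fitted to whatever 12-month surveys arrive, which is close to the repair proposed here. This is a possible reading. But the qualifier names no outcome, level or criterion. In an open-label trial that leaves the choice open until after the data are seen, and no other method is named.

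Three stronger readings are tempting and should not be taken.

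- *The method cannot be applied to the CAT at all.* True per patient only. A unit mean can be carried forward, and the primary plan is framed at unit level.
- *It always pulls effects to zero.* Only if the effect builds over time and missingness is similar between arms. The illustration with baseline copied is also the severe case: a 6-month survey is scheduled and would normally be the last observation. Nothing in the article suggests that 4 to 13 units will return no 12-month surveys.
- *The plan carries utilities past death and so distorts cost-effectiveness.* No passage says this. The economic section does not mention the method, and Table 2 anchors dead at 0. It is a risk left open, and a between-arm error needs mortality, or utilities before death, to differ between arms.

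It is also fair to say that patient-level identification of the EQ-5D-5L survey is not settled. The legend to Fig. 1 puts EQ-5D-5L in the same outcome survey as the anonymous CAT, while Economic evaluation says self-reported survey data will be linked.

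**Conclusion.** The point stands in this form. The article commits to one imputation method. For the primary outcome, its own anonymity statement rules that method out per patient and leaves only the copying of old unit means. This is a stated, inferior choice, not detail left to an analysis plan. The direction of bias cannot be known beforehand; under similar missingness and a growing effect it is toward zero. The illustrated sizes, 0.21-0.16 with baseline copied and about 0.22-0.20 with a half-developed 6-month value, rest on an assumed 10-30% of units copied equally across arms. They are not forecasts. For linked outcomes the conclusion is narrower: a weak single-imputation method, with the treatment of deaths not ruled in or out.

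**What to change.** Delete the sentence on last observation carried forward and replace it with:

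1. **Primary outcome.** Fit the mixed model to all CAT surveys received, without imputation. Include the 6-month surveys, for example in a repeated cross-section mixed model with time, arm by time, and random effects for unit and unit by time. Units with no 12-month surveys then still contribute. Other models that use all surveys would also serve.
2. **Patient-linked outcomes.** Use likelihood-based mixed models, or multiple imputation that respects unit and arm, and state which outcomes are in fact linkable.
3. **QALYs.** Count the EQ-5D-5L index as 0 after death where the date of death is available from records or linkage. The article does not list dates of death among the linked data, so availability should be confirmed.

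The cost is one paragraph of wording and slightly more modelling. Items 1 and 2 need no data beyond those already planned. The change should be made before the 12-month comparison is run.
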